#### Secondary outcomes

The trial has a number of secondary outcomes described in detail in the trial protocol.^17^ Cost-effectiveness analyses will be conducted for any reduction in three key secondary outcomes—underweight, wasting and infant mortality—where a significant impact on these outcomes is observed at the 0.1 level.

ICERs will thus be calculated for wasting, underweight and infant mortality, if a significant effect is observed at a p value of 0.1 or less. Estimates of life years saved will be calculated for infant mortality averted by the intervention if a significant finding is observed. Although no agreed DALY weight currently exists for undernutrition in any form, expected ‘DALYs averted’ will be modelled using mortality averted by the intervention if significant, and evidence from the wider literature about morbidity gains from averting stunting, wasting and underweight in young children.^31^

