In the India and Peru studies, cost-effectiveness analyses were conducted from the societal perspective. The India and Peru studies reported incremental cost-effectiveness ratios (ICERs) per case of stunting averted of $34.67^i^ and $55.16, respectively. The Peru study reported the cost per death averted at $1952. In Pakistan and Malawi, cost-effectiveness analyses were conducted from the provider perspective and as such their findings cannot be compared directly with the other two studies. They did, however, report a cost per disability-adjusted life year (DALY) averted of $12.20 and $42, respectively, which can then be compared with other ‘DALY averting’ interventions. In addition, the Pakistan study reported a cost per death averted of $406.

The proposed economic valuation of the CARING trial will be the first to assess the cost-effectiveness of combining participatory women's groups with home visits to reduce stunting. This economic evaluation will also employ a societal perspective, thus adding significantly to our understanding of the cost-effectiveness of this intervention and the likely fiscal space needed for its wider implementation. ICERs will be reported for cases of stunting averted, deaths averted and DALYs averted, in order to maximise comparability with other trials and ensure the usefulness of the economic evaluation as a resource allocation tool.

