### Study population

The CARING trial area includes 120 geographic clusters of around 1000 population, typically a village and any nearby hamlets. These clusters were purposively selected based on their population size. The study participants are pregnant women identified in the third trimester of pregnancy and all children born to pregnant women recruited between 1 October 2013 and 10 February 2015. Mothers and their children are followed up for a period of 18 months after the birth of the child.

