### Cost-effectiveness analysis

The cost-effectiveness analysis will be conducted as a within-trial analysis using the intention-to-treat results, and will be presented in terms of ICERs, calculated as the arithmetic mean difference in cost between the community intervention combined with VHNSC strengthening versus VHNSC strengthening only, divided by the arithmetic mean difference in effect.^37^
^44^

ICERs will be calculated for the primary outcome measure, that is, cases of stunting prevented, and for selected secondary outcomes and summary measures, including cases of wasting and underweight prevented, cases of infant mortality averted, life years saved and DALYs averted.

A number of sensitivity analyses will be carried out in order to assess the impact on the cost-effectiveness results, of changes in variables and parameters with the greatest uncertainty or with the greatest impact on the total costs. Cost-effectiveness acceptability curves will be generated to further describe uncertainty around the cost estimates.^45^

Costs will be presented in 2016 prices in Indian rupees and International Dollars (INT$). All costs will be adjusted for inflation using the Indian Consumer Price Index (CPI) and will be converted to 2016 INT$ using the 2016 Purchasing Power Parity (PPP) conversion factor for India. Moreover, costs and outcomes will be converted to present values using an annual discount rate of 3% in the base case, and annual rates of 0% and 6% in sensitivity analysis.

The affordability of the intervention will be explored using a range of criteria, including the WHO-CHOICE criteria,^46^ together with an analysis of fiscal space for programme delivery using a generalised fiscal space assessment method^47^
^48^ and probabilistic analyses to determine a set of cost-effectiveness thresholds.^45^
^49^ These analyses will also enable the exploration of a multicriteria decision analysis framework for resource allocation to this and other similar interventions to reduce stunting and wasting in young children.^50^ A wide range of affordability measures have been selected, in part, due to the paucity of evidence on the cost-effectiveness of comparable interventions. This precludes the use of simpler league tables and requires a wider range of affordability measures against which subsequent analysts may compare their own findings.

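### Deaths averted and life years saved rest on infant mortality although children are followed to 18 months, so deaths at 12–18 months are left out of the economic result

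*Protocol article*

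**What the plan says.** All references are to the protocol article.

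- **Secondary outcomes** limits the cost-effectiveness analyses of secondary outcomes to "three key secondary outcomes—underweight, wasting and infant mortality—where a significant impact on these outcomes is observed at the 0.1 level". Infant mortality is the only mortality outcome named there.
- The same section takes life years from that outcome: "Estimates of life years saved will be calculated for infant mortality averted by the intervention if a significant finding is observed".
- For DALYs the wording changes. They "will be modelled using mortality averted by the intervention if significant", without the word infant, and they add "evidence from the wider literature about morbidity gains from averting stunting, wasting and underweight in young children".
- **Cost-effectiveness analysis** lists, among the ICERs, "cases of infant mortality averted, life years saved and DALYs averted". It describes the analysis as within-trial and by intention to treat.
- **Economic evaluations of community interventions to improve children's growth** has no age limit: "ICERs will be reported for cases of stunting averted, deaths averted and DALYs averted". The **CARING trial** section likewise states an aim on mortality without restricting it to infancy.
- **Study population** gives the follow-up: "Mothers and their children are followed up for a period of 18 months after the birth of the child". The CARING trial section says home visits go to all children under 2.

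**The concern.** In its ordinary sense infant mortality stops at 12 months, and the article gives no other cut-off. Follow-up runs six months longer and exposure to the intervention also continues past the first birthday. Followed as written, the plan has three consequences.

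1. A difference between arms in deaths at 12–18 months, in either direction, does not enter deaths averted or life years saved.
2. A child who would have died at month 11 and instead dies at month 15 is scored as a death averted, although follow-up shows that the child died.
3. Stunting is assessed at 18 months. A child who dies at month 14 has no such measurement and is not an infant death, so that child appears in neither the stunting result nor the mortality result.

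Deaths, life years and DALYs are the measures the article relies on for comparison with other programmes. The article also names what should be one quantity in three ways (deaths, infant mortality, mortality) without stating one window, which leaves room to settle the window once results are known.

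**Working it through.** The article states no number of deaths, life years or DALYs, so there is no figure of its own to reproduce. The check sets the sections side by side and then sizes the omission under stated assumptions.

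**Side by side.** Life years and the mortality ICER use infant mortality (Secondary outcomes; Cost-effectiveness analysis). Follow-up is 18 months (Study population). The horizon is within-trial (Cost-effectiveness analysis). The unused window is therefore 12–18 months, and its deaths fall within follow-up.

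**Inputs from the article**
- 2,520 participants and 60 clusters per arm (Trial design), so 2,520 / 2 = 1,260 per arm. I assume one live birth per woman.
- Under-5 mortality U of 61 and 83 per 1,000 live births (Study setting).
- Base-case discount rate r of 3% (Cost-effectiveness analysis).

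**Assumptions, not in the article**
- Share of under-5 deaths in the first year, a: 70–90%.
- Share of the remaining under-5 deaths that fall at 12–18 months, f: 12.5% (spread evenly over the four years) to 30% (front-loaded).
- Remaining life L: 50–70 years.

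**Deaths per arm**
- Infant deaths = 1,260 × U × a. Low: 1,260 × 0.061 × 0.7 = 53.8. High: 1,260 × 0.083 × 0.9 = 94.1.
- Deaths at 12–18 months = 1,260 × U × (1 − a) × f. Low: 1,260 × 0.061 × 0.1 × 0.125 = 1.0. High: 1,260 × 0.083 × 0.3 × 0.3 = 9.4.

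**Share of all deaths by 18 months** = (1 − a)f / [a + (1 − a)f]; U cancels.
- Low: 0.0125 / 0.9125 = 1.4%.
- High: 0.09 / 0.79 = 11.4%.

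**If a share s of averted infant deaths is only postponed to 12–18 months,** deaths averted by 18 months are overstated by the factor 1 / (1 − s). Life years are overstated by nearly the same factor.

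| s | Factor |
|---|---|
| 5% | 1.05 |
| 10% | 1.11 |
| 20% | 1.25 |

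**Credit per postponed death.** Discounted life years = (1 − e^(−rL)) / r. With L = 50 this is 25.9 and with L = 70 it is 29.3. A child who in fact dies before 18 months lived less than 1.5 years. How far the credit is excessive depends on the life table, which the article does not give.

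**Opposite case.** If deaths at 12–18 months are also prevented, they are missing from the denominator and the ICER per death averted is too high.

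**The case against.** **The outcome is defined elsewhere.** The article refers secondary outcomes to the trial protocol, which is not shown, and that document may define mortality beyond infancy. This does not settle the matter, because the Secondary outcomes section itself fixes infant mortality as the input to life years.

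**Tying an ICER to a named trial outcome is normal.** This is true, and a reason to keep the infant-mortality ICER. It is not a reason to leave known later deaths out of life years.

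**DALYs.** A reader might infer that DALYs too are credited from infant mortality only. The text does not support that: the DALY sentence says mortality without an age limit and adds morbidity gains from the literature. It is only probable that the mortality part uses infant mortality, since no other mortality outcome is named for testing.

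**Size.** A reader might take a 20% reduction in infant deaths and a net shift of three deaths at 12–18 months, and infer a distortion of 18–25%. With 61 to 84 infant deaths per arm (a = 80%), a 20% reduction averts 12 to 17, and 3/17 = 18% and 3/12 = 25%. But ICERs and life years are calculated only "if a significant effect is observed at a p value of 0.1 or less". A two-sided two-proportion test ignoring clustering gives p = 0.24 for 61 against 49 deaths and p = 0.15 for 84 against 67. Clustering would ordinarily raise both. The article does not state sidedness; one-sided, only the second comparison would pass. Two-sided and unclustered, about 17 deaths averted (61 against 44) or 20 (84 against 64) are needed, each with p = 0.09. Three deaths are then 3/20 = 15% to 3/17 = 18%. The shift of three is itself arbitrary.

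**Life table.** One could say that every postponed death receives a full life expectancy. That depends on the method, which is not given, and a life table already carries average mortality after the first birthday. What it cannot carry is a difference between the arms.

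**Cost window.** Some costs are collected after 12 months, such as time use of mothers with children aged 13–18 months and the 18-month care-seeking survey (Table 1). It is tempting to infer that an 18-month death count would align costs and effects. It would not: programme costs include start-up and implementation of an intervention that serves all children under 2.

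**Conclusion.** The point stands in a limited form. As written, the mortality ICER and life years saved ignore deaths observed at 12–18 months and count an infant death postponed past 12 months as averted. The mortality part of DALYs probably does the same. No stated figure is contradicted.

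Under the assumed age pattern the omitted deaths are about 1–9 per arm, or 1–11% of deaths by 18 months. The effect is probably modest, and would be material only if the intervention mainly delays deaths or has a distinct effect after the first birthday. The article supports no claim that the bias runs one way. The size rests wholly on the assumed split of under-5 deaths by age, and the reading of infant mortality as under 12 months is the ordinary meaning, not a definition given in the article.

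**What to change.** State one mortality window and use it in the three places where the article names the quantity: the background section on economic evaluations, Secondary outcomes, and Cost-effectiveness analysis. Base deaths averted, life years saved and the mortality component of DALYs on all deaths from birth to the 18-month visit. Keep infant mortality, with its ICER, as the separately reported named trial outcome.

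Follow-up to 18 months is already planned, so no extra follow-up is needed. The cost is one additional effect estimate and test for 18-month mortality, and the 0.1 significance condition must be rewritten to say which mortality result governs life years and DALYs. The change does not make the death window match all programme costs, and the report should say so.

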### Equity impact

As the gains from such a complex intervention may not be equitably shared among the target population, the equity impact of the intervention will be analysed within the economic evaluation. Primary and secondary outcomes will be decomposed according to the socioeconomic status of ‘recipient households’ and the economic evaluation stratified accordingly. To account for the fact that many households in these districts will be asset or cash poor, a multidimensional poverty score will be used to define households' socioeconomic status.^32–34^ These stratified, subgroup analyses may enable us to further verify the argument by Carrera *et al*,^35^ that investing in the most deprived communities is more cost-effective than the same investment in less deprived communities.

#### Identification, measurement and valuation of resource use

These analyses will measure the cost-effectiveness of the intervention from a societal perspective. This perspective is the most comprehensive, taking into account costs incurred by the programme, implementing agencies or donors, providers and households.^36^ This perspective determines the time horizon of any modelling, the choice of costs and outcomes to be included in the analysis, and the measurement and valuation of costs and consequences of the intervention.^37^
^38^ In this section, we will describe in detail the proposed methods for measuring and valuing programme costs, provider costs and household costs. Programme costs include those incurred by the implementing agencies, that is, University College London, the Public Health Foundation of India (PHFI) and Ekjut (http://www.ekjutindia.org), a civil society organisation leading the study. The provider or health system costs are those incurred by MTCs, Primary Health Centres, community workers and VHSNCs. The household or user costs include those incurred by mothers and their families. Table 1 shows the flow of cost data collection described further below.

**Table 1 BMJOPEN2016012046TB1:** Steps in cost data collection

Cost category or perspective	Type of costs	Description	Source	Sample size
Project/programme	Direct	Costs of implementing the intervention	Project accounts of implementing agencies	N/A
Provider/health system	Direct	Costs of referrals made to MTCs	Project records for number of referrals, MTC costing study for unit costs of services	All referrals made in intervention and control clusters
	Indirect	Opportunity cost of increase in workload of CHWs	Time use survey with CHWs	A purposive sample of CHWs in both arms will be selected for time use interviews
		Opportunity cost of time spent by VHSNC members in meetings	Project records	All meetings held and number of people attending the meetings will be recorded
Patients/households	Direct	Household expenditure on food	Household consumption survey	A random subsample of 300 households
		Cost of care seeking for mothers and children	3-month and 18-month follow-up surveys with mothers	All participants in the study
	Indirect	Opportunity cost of participation in groups and home visits	Household time use survey	A random subsample of 120 mothers, with children aged 13–18 months
		Opportunity cost of changing health, nutrition or stimulation behaviour	Household time use survey	A random subsample of 120 mothers, with children aged 13–18 months

MTC, Malnutrition Treatment Centres; VHSNC, Village Health Sanitation and Nutrition Committee.

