### Aim and objectives

The aim of the CARING economic evaluation is to measure the cost-effectiveness of a community intervention that includes participatory learning and action with women's groups and home visits to improve the growth of children under 2. Activities to strengthen local VHSNCs will be undertaken in intervention and control arms.

The specific objectives of the economic evaluation are:
To measure the costs of setting up and implementing the community intervention to improve children's growth and the strengthening of VHSNCs.To estimate the costs to the health system, of (a) treatment for SAM provided at Malnutrition Treatment Centres (MTCs) or Nutritional Rehabilitation Centres (NRCs); (b) increased care seeking at Primary Health Centres for childhood illnesses, as a result of the programme.To measure the direct and indirect cost of the intervention to the health system, when existing community health workers may take on a greater workload resulting from the intervention.To measure the direct and indirect cost of the participation of community leaders or VHSNC members in participatory meetings or other activities related to the intervention.To calculate the household costs of care seeking related to undernutrition and any costs of changing feeding and caring behaviours, for example, the possible costs of buying additional/different foods.To estimate the incremental cost-effectiveness of the intervention combined with strengthening of VHSNCs, as compared with strengthening VHSNCs alone, where all new activities are delivered in addition to existing government programmes.

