### Study setting

As described fully in the trial protocol,^17^ the CARING trial takes place in West Singhbhum (Jharkhand state) and Kendujhar (Odisha state) districts in India. Odisha and Jharkhand are among the poorest states in India, with high rates of child mortality and undernutrition,^25^
^26^ and female literacy rates below 50%.^27^ In 2010, under-5 mortality was estimated 61 and 83 per 1000 live births in rural Jharkhand and Odisha, respectively.^28^
^29^ In Jharkhand over 50% of children are stunted, and in Odisha over 45% are stunted.^25^
^26^ The study districts are predominantly rural, with a combined total population of ∼3.3 million.^17^

Community-based health and nutrition services for mothers and children in the study villages are provided by three community workers: an Anganwadi worker (AWW), an Accredited Social Health Activist (ASHA) and an Auxiliary Nurse Midwife (ANM). AWWs provide supplementary nutrition to pregnant women, breastfeeding mothers and children aged 6 months to 6 years. ASHAs support community members in accessing essential healthcare services and promote institutional deliveries. ANMs provide services such as childhood immunisation and essential medicines. Community-based services are supplemented with care from primary care centres, MTCs that specialise in the treatment of SAM and hospitals.

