### Provider or health system costs

Provider costs or costs to the health system will be calculated for MTCs, Primary Health Centres, community workers and VHSNCs.

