#### Malnutrition treatment centres and primary health centres

MTCs provide care for SAM. Demand for these services may increase if SAM is better identified in the community and/or systems for referring children to MTCs are improved. Conversely, demand for these services may decrease if SAM is prevented by improved early child nutrition.

We will estimate any change in the demand for MTC services resulting from the intervention, and the concomitant value of any additional care provided. The trial's routine monitoring forms will capture the number of children admitted for SAM at MTCs. Differences in admissions between intervention and control areas will be attributed to the trial activities. Primary data on the average unit cost of care for SAM will be collected from the two MTCs in the project area. A simple cost-capture form was developed for facility data collection after an introductory meeting with centre managers. Data from the cost-capture form will be used to complement existing data from centre reports, patients’ records and published national and state reports relating to MTCs. Costs of services provided by the MTCs will be calculated using a step-down approach.^39^

For Primary Health Centres, any change in demand for primary care will be identified in the trial's routine monitoring forms as described above. Any cost of that change in demand will be calculated using published data on the unit costs of treatment at Primary Health Centres.^43^

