### Household or user costs

CARING may influence household costs in a number of ways. Changes in the quantity, variety or quality of food fed to pregnant women and young children, may increase household expenditure on food. The intervention may also increase care seeking. The effect on health spending of this change may be positive or negative. Increases in care seeking from a very low base may increase total spending on care. Conversely, a shift from curative to preventive care seeking may decrease spending on care. Similarly, improved early child nutrition that averts severe malnutrition and related illnesses, may also reduce the need for care seeking. Finally, as the intervention seeks to change health and nutrition-related activities, it may also change the allocation of time to these activities. Participation in women's group meetings and in home visits will also have a direct time ‘cost’.

Changes in food expenditure are measured with a comprehensive household consumption and expenditure survey conducted on a random subsample of 300 households (150 per trial arm). The consumption and expenditure model is conducted twice for each participating household, with the two data collection points 1 year apart. This allows the measure of interest to be the change in expenditure over a 1-year period, with that change compared between intervention and control areas.

Changes in health spending are measured with a set of questions on care seeking collected from all the mothers recruited in the project. Care seeking data are also collected at two time points in the trial; first when the pregnant mother is recruited and again when the baby is 18-month old. In this instance, the measure of interest is not the change in spending over that time period, but a comparison of absolute levels of spending between intervention and control families with children of the same age.

Finally, the time cost of group participation, participating in the actions taken by the group, engaging with home visits or changing health, nutrition or stimulation behaviours will be measured using a time use survey to be conducted on a subsample of 120 women, equally distributed across the intervention and control arms.

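### Provider costs omit hospital care outside the Malnutrition Treatment Centres, so a shift between levels of care is costed on one side only

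*Protocol article*

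**What the plan says.** All references are to the Protocol article. Under Identification, measurement and valuation of resource use, the analysis is societal, and that perspective is described in these terms: "This perspective is the most comprehensive, taking into account costs incurred by the programme, implementing agencies or donors, providers and households". The same section then defines the provider side: "The provider or health system costs are those incurred by MTCs, Primary Health Centres, community workers and VHSNCs". The section on provider or health system costs repeats the list: "Provider costs or costs to the health system will be calculated for MTCs, Primary Health Centres, community workers and VHSNCs".

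The Study setting section describes a wider set of facilities: "Community-based services are supplemented with care from primary care centres, MTCs that specialise in the treatment of SAM and hospitals".

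The health-system objective has two parts. The first is treatment of severe acute malnutrition (SAM) at MTCs or Nutritional Rehabilitation Centres. The second is "increased care seeking at Primary Health Centres for childhood illnesses, as a result of the programme". On use of inpatient care, the costing methods say: "The trial's routine monitoring forms will capture the number of children admitted for SAM at MTCs".

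On the household side: "Changes in health spending are measured with a set of questions on care seeking collected from all the mothers recruited in the project". Table 1 lists the cost of care seeking for all participants and does not restrict it by type of facility.

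**The concern.** The protocol names three kinds of facility behind the community workers: primary care centres, MTCs and hospitals. It costs the first two on the provider side and omits the third without comment. The household costs section expects the intervention to change care seeking in either direction: upward from a low base, or downward as severe malnutrition and related illness are averted.

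If earlier primary care replaces some hospital care, the plan adds the primary care cost and misses the hospital saving. If better recognition of illness sends more children to hospital, the plan misses the added cost. In both cases the incremental cost, and so every ICER built on it, reflects part of the change in provider resources. The planned sensitivity analyses vary the inputs of the model. Hospital provider cost is not described as an input, so as written they would not reveal the gap.

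**Working it through.** The protocol gives no figure to reproduce. The check sets the costing rules side by side and then writes out what is missing.

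**Step 1. What is costed for each level of care.**

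| Level of care | Source for use | Source for provider unit cost | In provider costs? |
|---|---|---|---|
| MTCs (SAM admissions) | Routine monitoring forms | Primary data from the two MTCs in the project area | Yes |
| Primary Health Centres | Routine monitoring forms | Published unit costs | Yes, in the text; no row in Table 1 |
| Hospitals outside MTCs | None described | None described | No |

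**Step 2. Is the list closed?** The neighbouring sentences on programme and household costs are worded as non-exhaustive. The provider sentence is worded as a definition, and the later section repeats the same four items. The objectives and the costing subsections add no hospital item. Absence from Table 1 is weak evidence by itself, because Primary Health Centres have no row there either. The two matching lists carry the point.

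**Step 3. Could the detail sit elsewhere?** The CARING trial section refers the trial design to another paper, but says that the purpose of this article is to set out the economic methodology in full. A cost boundary that is stated twice is not a detail lost in condensation.

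**Step 4. What the household data cover.** They can capture what a family pays at a hospital. They do not value the resources that the hospital uses and does not recover from the family. The protocol accepts this distinction, since it costs MTCs and Primary Health Centres separately from family spending.

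**Step 5. The missing term.** Let Δh be the difference (intervention minus control) in non-MTC hospital episodes per child, c the provider's cost per episode, and p the family's payment to the hospital per episode, assumed to be captured in household costs. Then:

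- missing incremental cost per child = Δh × (c − p)
- ICER as planned = ICER with hospital care − Δh × (c − p) / ΔE, where ΔE is the difference in effect per child

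With ΔE above zero and c above p, the plan understates the ICER if Δh is positive and overstates it if Δh is negative. Where family payments cover the full cost (c = p), nothing is missing.

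**Step 6. A shift between levels.** Suppose s episodes per child move from hospital to a Primary Health Centre with provider unit cost u. The change in provider cost, net of family payments to the hospital, is s × u − s × (c − p). The plan counts s × u only.

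The protocol gives no value for Δh, c, p, u or s, so no number can be put on either expression.

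**The case against.** The best defence is that this is a choice of scope. The health-system objective names SAM treatment and Primary Health Centre care, and the costing sections follow it. Hospitals appear once, as background. The facility service closest to the intervention, inpatient care for SAM, is costed with primary data, and families' hospital payments can enter through the care-seeking questions. All of that stands. It narrows the gap to unrecovered provider cost at hospitals outside MTCs, but does not close it or explain why the other two levels are costed and this one is not.

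Three stronger readings are tempting, and the document does not support them.

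- *The plan breaks its own claim to be comprehensive.* That phrase describes the societal perspective in general and lists who bears costs. It does not promise that every type of facility is costed.
- *All hospital care enters at zero.* SAM inpatient care at MTCs is valued, and family payments elsewhere are eligible to be counted.
- *The omission is known to be large.* The protocol gives no admission rate or unit cost, and nothing in it shows that hospital admissions are among the costliest events. One could assume a between-arm difference of 2 to 5 admissions per 100 children. With 2520 participants assumed to split equally (2520 / 2 = 1260 per arm), that is a difference of 0.02 × 1260 ≈ 25 to 0.05 × 1260 = 63 admissions. With no base rate or unit cost behind it, this says nothing about the ICER.

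**Conclusion.** The point holds as a one-sided omission in the cost boundary. Followed as written, the plan values changes in MTC and Primary Health Centre demand but gives no provider cost to changes in other hospital care, beyond what families pay. Size and sign are unknown: they depend on Δh and on c − p, and the protocol gives neither. That no value is assigned is an inference from the closed list and the absence of any hospital item; the protocol does not say so outright. The conclusion also assumes that family payments do not fully cover hospital costs. The omission should be corrected or openly justified, but the document does not show that it would change the conclusion on cost-effectiveness.

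**What to change.** Add non-MTC hospital care to the provider cost list and to Table 1. Take hospital contacts by arm from the routine monitoring forms or from the care-seeking questions put to all mothers, whichever records the type of facility. The protocol does not show the content of either, so check this first. Check also which periods the questions cover: Table 1 places them at 3 and 18 months, while the household costs section places them at recruitment and 18 months.

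Value the contacts with published unit costs, as is already planned for Primary Health Centres, net of household payments so that the same cost is not counted twice. Vary both use and unit cost in sensitivity analysis.

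If neither source records hospital use, run a scenario range for Δh and c − p and describe the provider costs as excluding hospital care outside MTCs.

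Where a source exists, the cost is one more unit-cost source and one more line in the costing sheet. The downside is reliance on published unit costs and, if the mothers' questions are used, on recall. Primary Health Centre use comes from monitoring forms, so it sets a precedent for the unit costs but not for recall.
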